## Abstract

**Background:**

Violence against women is a well understood devastating global pandemic, and human right violation. One in three women experienced intimate partner violence worldwide. In Ethiopia, the level of domestic violence against women is one of the highest in the world. However, Ethiopia is signatory for various conventions and incorporated in legal frameworks. Nevertheless, effective implementation of the existing policy documents, and engaging different stakeholders is very limited. Therefore, we aimed to pilot feasibility of implementing available research evidence and policy documents at community level to prevent domestic violence against women in Awi zone, northwestern Ethiopia.

**Methods:**

A community-based quasi-experimental study design will be employed using mixed method. Multistage stratified systematic sampling and purposive sampling will be used to recruit quantitative and qualitative study participants, respectively. A total of 1,269 women will be participated in the intervention, active comparator and control groups. Pre and post-test quantitative data will be collected using face-to-face interview. Qualitative data will be collected through in-depth, key informant interview and focus group discussions. Intervention: advocacy meeting will be held to persuade local politicians and sustain the implementation of community based intervention to prevent domestic violence against women. Community representatives will be trained to enhance peer education to promote community awareness and engage stakeholders to transform the traditional gender norm within local context. Awareness creation and husband involvement will be made through integrating the intervention with community health extension program. Only husband involvement will not be promoted in the active comparator to test the role of husband involvement on the domestic violence prevention activities. Intervention progress will be monitored regularly. Gathered data will be entered in Epidata and exported to SPSS (23.0) software for analysis. Descriptive statistics, logistic regressions, intention to treat analysis and difference in differences will be computed. Qualitative data will be transcribed, color coded, thematically analyzed and arranged using Nvivo.

**Discussion:**

This interventional study is aimed to design, pilot and translate proven research evidence, agreed conventions and country policy document to real setting implementation. We are expecting to initiate implementation of culturally acceptable intervention through engaging stakeholders. Policy makers, planners and any concerned bodies will be benefited.

**Trial registration:**

ClinicalTrials.gov ID: NCT03265626

## Plain English summary

Violence against women is a well-recognized reproductive health issue. It is a cross-cutting issue which is interlinked with every day’s routine activity and overall development agenda in the world. Several primary studies have been conducted on the area that briefly report the level and associated factors of the domestic violence against women. Moreover, some interventional studies also conducted in different parts of the world revealed that interventions mainly focused on gender norm, societal culture and other behavioral change communication can improve the prevention strategies to tackle domestic violence against women. Nevertheless, many countries still have a limited motivation to implement their policy in real setting to prevent violence against women. One of the most dilemmatic issue is considering violence against women as a private matter, and still there is lack of clear understanding on the difference of private and public matters. Therefore, this study aims to mobilize community to prevent domestic violence against women. It will contribute evidence to program planners, policy makers, clinicians and other stakeholders to have informed decision on the issue of domestic violence against women.

## Background

Gender based violence against women is a well-recognized public health problem, gross pervasive abuse of human rights, and major obstacle for achieving the sustainable development goals worldwide [1–6]. Globally, one in three women experience violence against women (VAW) [4, 7, 8]. About 38–60% of murders of women are committed by intimate partners every year. Domestic VAW is not only an exhibit of unbalance of power, and a bad women’s life experience at their home [9, 10], it accounts for 5% loss of women’s healthy years. The morbidity and mortality due to VAW is more than a cumulative burden of cancer, road traffic accidents and malaria, a huge threat and unmanageable global burden to public health for the future [10]. According to World Health Organization (WHO) multicounty study indicated that intimate partner violence in Ethiopia was 71%, which is the highest in the world [11]. Research evidence show that domestic violence is strongly linked with gender inequality that affect women’s ability to have a discussion on several reproductive health issues including human immunodeficiency virus (HIV) and negotiate on condom use [12–14]. The cost of VAW is estimated from 1.2–3.7% of the country’s gross domestic product, which is equivalent to what many governments spend on primary education [8]. Nevertheless, most governments have considered domestic VAW as minor social tricky, private matter and not taken as crime [1, 10, 12].

The United Nations aims to create an enabling household environment, improve women’s right, political, economic empowerment and legal protection [15]. Consistently, the Maputo Plan of Action (2016–2030) gives due attention to the implementation of international, regional and national legislations to tackle VAW [16]. On the other hand, a systematic review suggested that women empowerment and community mobilization averted $13–19 per disability adjusted life year. Hence, gender responsive interventions that target traditional gender norms, behavior change communication and structural drivers are cost effective approaches to prevent VAW [17]. Likewise, domestic VAW is strongly associated with gender norms, poverty, denied access to education, embedded in social customs, lack of autonomy, inequitable gender attitudes, women accept justified wife beating and alcohol use [1, 2, 5, 18–23].

Moreover, domestic VAW is significantly associated with various poor health outcomes (low birth weight, premature birth, malnutrition, suicide, homicide, mental illness, physical injuries, disability and non-communicable diseases) [1, 6, 7, 18, 20, 24–29]. In addition, VAW has been associated with HIV and other sexual transmitted infections (STIs) acquisition, unintended pregnancy, induced abortion and other poor reproductive health conditions [1, 5, 7, 10, 14, 19–21, 23, 27, 30–43]. It is a cross cutting issue which requires comprehensive approach to address it (microfinance support, equality norm or culture transformative training; communication skill in relationship; minimize access to alcohol use and community health education [1, 20, 44]. The conceptual framework that shows the detail of factors associated with domestic VAW included as an additional file (Fig. 1).

**Fig. 1 Fig1:**
[figure not shown]
Conceptual framework adapted from ecological model

In Ethiopia, domestic VAW is a common women’s life experience. A systematic review on studies done in Ethiopia (2000–2014) indicated that any intimate partner violence (IPV) is a known phenomenon in the country which ranged from 20 to 78% [45]. In response to this, the government of Ethiopia has incorporated the issue of women’s right and gender equality in the constitution (Article 35 and 89(7)) [46], criminal code under proclamation NO.414/2004 *(Article 564*) [47] and Family Code Proclamation No. 213/2000 [48]. Violence against a marriage partner or a person cohabiting in an irregular union is prohibited. In addition, access to and control over resource including other rights and responsibilities of partners in marriage or cohabitation are clearly addressed in the policy documents. Moreover, Ethiopian Ministry of Health has developed a standard operating procedure for the response and prevention of sexual violence in Ethiopia in 2016 [49]. Community mobilization, stakeholder engagement and partner involvement are the most prioritized intervention programs which need effective implementation, but these are still very limited. Furthermore, this implementation research will give an insight to mobilize resource, involve stakeholders to put the existing law and regulations into action and identify implementation bottlenecks. Given the paucity of evidence, it will provide information on feasibility and implementation of community based preventive intervention programs.

### Study objective

The overall aim of this study is to assess the outcome of community based intervention to prevent domestic violence against married or cohabiting women in the reproductive age and associated factors in Awi zone of the Northwestern Ethiopia from November 15, 2017 to November 15, 2018**.**

### Specific objectives

To assess the baseline level of domestic VAW in the study areaTo identify associated factors of domestic VAW in the study areaTo explore implementation bottlenecks in VAW program in the study areaTo implement culturally acceptable interventions to address domestic VAWTo assess the outcome of community based intervention on domestic VAW

## Methods

### Study setting

This study will be conducted in Awi zone, Amhara regional state, Northwestern Ethiopia. Enjibara town is the administration center of Awi zone which is located 447 km from Addis Ababa. Based on the 2007 Census, it has a total population of 982,942 and 491,077 of them are women. Only 12.5% of population are based in urban. Based on the preliminary assessment; Awi zone administration has nine districts with a total of 204 sub-districts and 6463 development armies. *Sub-district is the smallest administrative unit which has an estimated 1000–1500 households or 5000 total population*. In one of the district of the Awi zone, Faggetalekoma district has one of the highest record in domestic VAW [45, 50]. The women and children affair office has structured by the government to execute such type of issues. The zonal health department and district health offices have been implementing the standard operating procedures to respond and prevent sexual violence.

### Study design and participants selection

Community based three arm quasi-experimental design will be employed usingquantitative and qualitative techniques (mixed methods).

### Quantitative study participants

Married or cohabiting women (15–49 years) will be recruited for the quantitative study. Study participants will be allocated into intervention, active comparator and control groups. Three districts will be selected out of nine districts considering stability or mobility status, convenience to implement intervention and monitor the control. The study design and participant allocation is illustrated as an additional file (see Fig. 2).

**Fig. 2 Fig2:**
[figure not shown]
Illustration of quasi-experimental design for intervention implementation

### Qualitative study participants

Community representatives (local leaders, religious leaders and elders), husbands, health care providers, police and women affair office representatives will be involved.

### Inclusion criteria

Women (15–49 years) from the general populationMarried/cohabited women who have stayed at least 12 months with the current husbandWomen and community representatives who have registered or recognized as permanent resident at least for 6 months

### Exclusion criteria

Women and or community representatives who will unable to respond due to severe physical or mental illness

### Sample size determination

The sample size is determined considering both the intervention and control using a formula recommended for dichotomous outcome variable. We assumed that implementation of community based intervention program to prevent domestic VAW is superior as compared with the standard service [51]. In addition, we considered 5% margin of error, 95% significance level and 80% power.$$ N=2\times {\left(\frac{z_{1-\alpha }+{z}_{1-\beta }}{\mathrm{d}\hbox{-} {\delta}_0}\right)}^2\times p\times \left(1-p\right) $$

Where as; N is the sample size of each group, P is prevalence in standard intervention (control arm), d: the real difference between two treatment effects (d = P_o_-P_x_); 22%–9% = 13% = 0.13: study done in Uganda (22%) in the standard intervention group [52]; δ_0:_ statistical acceptable margin (5%); ɑ: significance level at 95% (ɑ = 1–0.95 = 0.05 = 1.645), ß_:_ 80% power (ß = 1–0.8 = 0.2 = 0.845. Then, 15% is added for potential non-achievements. Furthermore, due to the multistage sampling, design effect is considered to boost the power and precision that taken from the design effect of women experienced physical or sexual violence in the study area (Amhara region) in the last 12 months was 1.11 [53]. Eventually, a total 1269 women is obtained for the three arms (i.e. 423 for each group). The number of qualitative study participants will be determined by information saturation. However, a minimum 12 in-depth interviews and two focus group discussions (FGDs) (male versus female groups) which comprise 8–10 discussants will be conducted.

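### The sample size formula gives both arms the control arm's variance, so on the plan's own inputs 423 per arm has about 89% power rather than 80%: a minor error on the safe side

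*Protocol article*

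**What the plan says.** Everything is in the protocol article, Methods, Sample size determination. The printed formula is N = 2 × ((z₁₋α + z₁₋β)/(d − δ₀))² × p × (1 − p), where N is the size of each group. The single prevalence p is tied to one arm, while d involves both: "P is prevalence in standard intervention (control arm), d: the real difference between two treatment effects (d = P" (the subscripts follow in the source). The control figure is borrowed: "study done in Uganda (22%) in the standard intervention group". The difference d is the control prevalence minus the other arm's prevalence, 22% − 9% = 13 points.

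The remaining inputs are:
- the margin δ₀: "statistical acceptable margin (5" percent;
- the significance level: "significance level at 95% (ɑ = 1–0.95 = 0.05 = 1.645";
- the power: "80% power (ß = 1–0.8 = 0.2 = 0.845".

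A 15% allowance and a design effect of 1.11 are then applied. The result is stated as "Eventually, a total 1269 women is obtained for the three arms (i.e. 423 for each group", and the section presents this as the number for 80% power: "In addition, we considered 5% margin of error, 95% significance level and 80% power".

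**The concern.** The 9% is never labelled as the intervention prevalence. But d is control minus the other arm and 22% is the control arm, so no other reading is available. That 9% enters the formula only through d. The variance factor 2p(1 − p) uses 22% twice, which is the variance of a difference between two arms that both have 22%. The section therefore assumes one alternative for the effect and another for the variance, and the printed 80% belongs to neither a 22%-against-9% comparison nor any other that the plan describes.

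What is at stake is the accuracy of the power statement. Number enrolled, conduct and analysis are not affected.

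**Working it through.** **Inputs, all from Sample size determination.** Control 22%; intervention 9%; d = 0.13; δ₀ = 0.05, so d − δ₀ = 0.08; z = 1.645 (one-sided 5%); z for 80% power 0.8416 (printed as 0.845); allowance ×1.15; design effect ×1.11; final n = 423 per arm.

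**1. Reproduce the plan's figure.**
- Variance factor: 2 × 0.22 × 0.78 = 0.3432.
- Before inflation: ((1.645 + 0.8416)/0.08)² × 0.3432 = 331.5.
- After inflation: 331.5 × 1.15 × 1.11 = 423.2, which matches the printed 423. With the rounded 0.845 the two results are 332.5 and 424.4.
- Other routes fit less well: dividing by 0.85 in place of multiplying by 1.15 gives 433 to 434, and a two-sided 5% level gives 537.

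So the printed number comes from p = 0.22 in both arms.

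**2. Variance under the stated alternative.**
- 0.22 × 0.78 + 0.09 × 0.91 = 0.1716 + 0.0819 = 0.2535.
- 0.2535/0.3432 = 0.74, so it is 26% smaller.
- Other usual choices do not give 0.3432 either. The average prevalence of 15.5% gives 2 × 0.155 × 0.845 = 0.262. The null boundary of 22% against 17% gives 0.1716 + 0.1411 = 0.3127.

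**3. Power of 423 per arm, one-sided 5%, 5-point margin.** Undoing the plan's own inflation leaves 423/1.15/1.11 = 331.4 effective women per arm. Power is Φ(0.08/SE − 1.645).
- Plan's variance: SE = √(0.3432/331.4) = 0.03218; 0.08/0.03218 − 1.645 = 0.841; power 80.0%.
- Variance for 22% against 9%: SE = √(0.2535/331.4) = 0.02766; 0.08/0.02766 − 1.645 = 1.247; power 89.4%.
- If 15% of the 423 are lost, 423 × 0.85/1.11 = 323.9 effective; power 88.8%.

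Cross-checks: the Farrington–Manning restricted variance also gives 89.4% and 88.8%. Simulation with 400,000 trials gives 88.9% at n = 324 and 89.8% at n = 332.

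**4. Number needed for 80% with the correct variance.** ((1.645 + 0.8416)/0.08)² × 0.2535 = 244.9; × 1.15 × 1.11 = 312.6, so 313 per arm (939 in total). With the rounded 0.845 it is 313.5, so 314 per arm.

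**5. How far 89% depends on the other inputs.**

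| Change, correct variance kept | Power |
|---|---|
| None (331.4 effective) | 89.4% |
| 15% of 423 lost (323.9 effective) | 88.8% |
| Two-sided 5%, same margin: 0.08/0.02766 − 1.960 = 0.932 | 82.4% (81.6% at 323.9) |
| All 423 evaluable, design effect 1.11 | 92.7% |
| All 423 evaluable, no design effect | 94.8% |
| Two-sided 5%, null of zero difference | over 99% |

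**The case against.** The strongest reply is that this is a simplification, not a slip. The formula is printed openly, p is defined openly, and the arithmetic follows to 423. A single-prevalence formula that overstates the variance can only enlarge N here, so the plan delivers at least the 80% it sought. That stands as to direction and consequence. It does not make the power statement right. The section does not offer the variance term as a safety allowance; it has separate, explicit allowances of 15% and 1.11. And one prevalence is a poor stand-in for two that differ by a factor of about 2.4 (22/9).

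A second reply is that 89% is itself fragile. This also stands. It rests on the one-sided level and the margin, whereas the section on data processing and statistical analysis judges the effect by a 95% confidence interval and P below 0.05, with no mention of a one-sided test or a margin. With a two-sided 5% level and the same margin the power is about 82%, close to the printed figure. The 89% also carries the 1.11 design effect and the borrowed 22% unchanged. Printed bare, it would promise more than has been shown.

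A reader might infer three further things that the document does not support:
- That the smallest detectable difference is misstated as 13 points. The section gives 13 points as the assumed true difference and never calls it the smallest detectable one.
- That other power figures are affected. This is the only power statement in the article, and no later recalculation is planned in it.
- That the trial is underpowered because its formula is wrong. On this term the opposite holds.

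**Conclusion.** The point holds as a minor one. The variance term contradicts the prevalences assumed beside it, so the printed power does not match the printed inputs. On those inputs 423 per arm gives 88.8% to 89.4% power, not 80%, and 80% would need about 313 per arm. The conclusion assumes 22% and 9% are the true prevalences, a one-sided 5% test against a 5-point margin, the 15% allowance and a design effect of 1.11. It does not establish that those inputs are suitable, nor what power the difference-in-differences analysis would have. It is also no ground for reducing enrolment to 313, because the surplus exists only if every other input is right.

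**What to change.** In the sample size section, replace 2 × p × (1 − p) with p₀(1 − p₀) + pₓ(1 − pₓ), with p₀ = 0.22 and pₓ = 0.09, and label the 9% as the assumed intervention-arm prevalence. Keep 423 per arm. Restate the power along these lines: under a one-sided 5% test against a 5-point margin, with the 15% allowance and a design effect of 1.11, 423 women per arm give about 89% power for 22% against 9%; with a two-sided 5% test and the same margin the figure is about 82%. The conditions should stay attached to the number wherever it is quoted.

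The cost is one corrected formula and one restated sentence, with no change to enrolment or conduct.

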
### Data processing and statistical analysis

Both baseline and endline data will be checked and edited for completeness and consistency at field as well as at office. Explanatory and outcome variables will be clearly predefined prior to data entry, in which domestic VAW will be coded as if a woman reports at least one type of experience of either physical, psychological or sexual violence coded as “Yes = 1” and “No = 0”. Similar coding will be done for physical, sexual and psychological domestic violence against women to carry out subgroup analysis. On the other hand, women’s wife beating accepting attitude will be measured using six questions or measurements, and also if women respond at least one justifying wife beating [58, 59, 61]. Similarly women autonomy will be measured in four indicators such as economic decision-making, reproductive health service utilization decision-making, extent of freedom of movement, and women’s attitudes toward violence [54].

Then, data will be entered in Epidata (3.5.1) and exported to SPSS (23.0) for further cleaning and analysis. Multiple imputation will be done to handle missing data as necessary. Descriptive statistics, binary and multiple logistic regressions and Intention to Treat Analysis (ITTA) will be computed. Moreover, Difference in Differences (DID) will be calculated to determine the net intervention effect. Finally, statistical significance of intervention effect will be measured using adjusted prevalence ratio, adjusted odds ratio/risk ratio at 95% confidence interval (CI) and *P*-Value less than 0.05. On the other hand, qualitative data will be transcribed through playing and replaying the voice recorder and also narrating the note taken during interviews or FGDs. The voice recorder audio will be listen as much as possible in quiet place. It will be transcribed independently by research assistant and principal investigator according to the verbatim of participants'. Then transcribed qualitative data will be translated from local language (Amharic) to English. The quotes will be narrated and cited using participant’s code. Thematic areas will be identified and arranged based on their themes. Ideas will be color coded, and then merged accordingly. Qualitative data will be analyzed or arranged using Nvivo software.

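### The sample size rests on a one-sided, endline-only test of benefit beyond a 5-point margin, but the analysis is a difference in differences judged by 95% CI and P < 0.05 with no margin, so the stated 80% power does not describe it

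*Protocol article*

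**What the plan says.** **Sample size determination (protocol article).** The section sets out a superiority aim: "We assumed that implementation of community based intervention program to prevent domestic VAW is superior as compared with the standard service". It lists "5% margin of error, 95% significance level and 80% power". The formula for each group is N = 2 × [(z(1−α) + z(1−β)) / (d − δ0)]² × p(1−p). Here α is converted to 1.645, β to 0.845, p is the control prevalence from a "study done in Uganda (22%) in the standard intervention group", d is 22% − 9% = 13 points, and δ0 is the "statistical acceptable margin (5", that is 5 points. Then "15% is added for potential non-achievements", and a design effect is applied from a regional figure that "in the last 12 months was 1.11". The result is 423 per arm and 1,269 in all.

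**Data processing and statistical analysis (protocol article).** Two statements bear on the treatment effect: "Difference in Differences (DID) will be calculated to determine the net intervention effect", and "statistical significance of intervention effect will be measured using adjusted prevalence ratio, adjusted odds ratio/risk ratio at 95% confidence interval (CI", with a P-value threshold of 0.05. Neither the 5-point margin nor a one-sided test appears there.

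**Monitoring and evaluation table.** The same women are to be interviewed again at endline, and DID is listed again as an endline task.

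**The concern.** The two sections describe different tests, in three respects.

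- **Sidedness.** The sizing uses 1.645, the one-sided 5% value. A 95% CI with P < 0.05 is ordinarily two-sided.
- **Null value.** The sizing asks whether the benefit exceeds 5 points. A ratio with its CI is ordinarily compared with no effect.
- **Estimand and variance.** The sizing uses the variance of one two-group comparison at a single time. A DID uses two waves, and its variance depends on the baseline prevalence and the within-woman correlation.

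What is at stake is the meaning of a positive result. The protocol foresees scale-up if the intervention works. A reader who takes the 5-point margin in the sizing as the benefit worth showing would not learn from P < 0.05 whether it had been exceeded. The quoted power also cannot be attached to the analysis that will be reported.

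**Working it through.** **1. Reproduce the plan's figure.** Inputs from the sample size section: p = 0.22, p(1−p) = 0.1716, d = 0.13, δ0 = 0.05, z values 1.645 and 0.845, inflation 1.15 and 1.11.

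N = 2 × (2.490 / 0.08)² × 0.1716 = 332.5; × 1.15 × 1.11 = 424.4. Truncating at each step gives 332 → 381 → 422.9, so 423. The figure reproduces.

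**2. Same formula, other readings.**

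- Two-sided with the margin: 2 × (2.805 / 0.08)² × 0.1716 = 421.9; × 1.15 × 1.11 = 538.6 per arm.
- Two-sided without the margin: 2 × (2.805 / 0.13)² × 0.1716 = 159.8; × 1.15 × 1.11 = 204 per arm.

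Of these readings, only the one-sided test with the margin gives 423.

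**3. Endline-only power and thresholds at 423 per arm.** Effective size is 423 / (1.15 × 1.11) = 331.4. With the plan's variance, SE = √(2 × 0.1716 / 331.4) = 0.0322.

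- One-sided with margin (the sizing): Φ(0.08/0.0322 − 1.645) = 80%.
- Two-sided against zero: Φ(0.13/0.0322 − 1.96) = 98%.
- Two-sided with margin: Φ(0.08/0.0322 − 1.96) = 70%.
- Observed difference needed, sizing rule: 0.05 + 1.645 × 0.0322 = 10.3 points.
- Observed difference needed, two-sided against zero: 1.96 × 0.0322 = 6.3 points.
- Chance of significance against zero if the true benefit is exactly 5 points: Φ(0.05/0.0322 − 1.96) = 34%.

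**4. DID.** The documents give neither a baseline prevalence by arm nor a within-woman correlation r. I assume 22% at baseline in both arms, 22% and 9% at endline, and a range for r. With 0.09 × 0.91 = 0.0819,

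variance = [2(1−r) × 0.1716 + 0.1716 + 0.0819 − 2r × √(0.1716 × 0.0819)] / 331.4.

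| Assumed r | SE | Threshold against zero, two-sided (points) | Threshold with margin, one-sided (points) | Power against zero, two-sided | Power with margin, two-sided |
|---|---|---|---|---|---|
| 0 | 0.042 | 8.3 | 12.0 | 87% | 47% |
| 0.3 | 0.036 | 7.0 | 10.9 | 95% | 61% |
| 0.5 | 0.030 | 6.0 | 10.0 | 99% | 75% |
| 0.7 | 0.024 | – | – | >99.9% | 92% |

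These figures are on the percentage-point scale. The analysis section judges adjusted ratios, so they approximate those tests.

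**The case against.** **The analysis section does not write out its null or its sidedness.** This is true. Two-sided against no effect is the ordinary reading of a ratio with a 95% CI and P < 0.05, and the point rests on that reading. Even without it, the margin is absent from the analysis and the sizing contains no DID variance.

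**No stated success rule is broken.** This also stands. A reader might infer that the protocol promises a benefit above 5 points and then fails to test it. The text says only that the intervention is assumed superior, and it uses 5% both for a margin of error and for the acceptable margin. The rule of exceeding 5 points is deduced from the formula; it is not a declared criterion. What can be said is that the power was computed for that rule.

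**The trial may look underpowered.** A reader might infer this from the 70% in step 3 or the 47% to 75% in step 4. The documents do not support it. Those figures combine the margin of one section with the two-sided rule of the other, and no section plans that combination. Against zero, 423 per arm is about twice the 204 that the formula needs, and even a DID with zero correlation has about 87% power. Because the same women are re-interviewed, zero correlation is a worst case.

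**A later analysis plan could settle it.** It could fix the analysis, but both rules already stand in this article, and one 80% figure cannot describe both.

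**Conclusion.** The point holds as an inconsistency between sections. It is not an arithmetic error, since 423 reproduces. The 80% power is for a one-sided, endline-only test against a 5-point margin. The planned analysis is a DID judged by 95% CI and P < 0.05 without that margin.

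The consequence is one of interpretation. Significance would not show that the benefit exceeds 5 points. Endline-only, results between about 6.3 and 10.3 points would be significant yet fall short of the sizing rule. As DID, the corresponding windows are 8.3 to 12.0, 7.0 to 10.9 and 6.0 to 10.0 points at r = 0, 0.3 and 0.5.

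All figures take the plan's 22% and 9%, its 15% allowance and its design effect of 1.11 at face value. The DID figures also rest on the assumed equal baselines and correlations. The endline figures keep the plan's variance, which uses 22% in both arms. With 9% in the intervention arm, SE = √((0.1716 + 0.0819) / 331.4) = 0.0277, and two-sided power with the margin is about 82% instead of 70%.

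**What to change.** State one hypothesis, one sidedness and one primary effect measure, in the same words, in both sections. Keep 423 per arm as a fixed size and replace the derivation with a power statement for the planned analysis. Replacing 1.645 by 1.96 in the formula is not enough, because it then gives about 539 with the margin or 204 without, and never 423.

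- **Simplest route.** Delete the margin and state a two-sided 5% test of no effect. Power is about 98% endline-only, or about 87% / 95% / 99% as DID at assumed r = 0 / 0.3 / 0.5.
- **If the margin is kept.** Write it into the analysis section as the success rule, so that the CI must exclude a benefit of 5 points or less. Restate two-sided power as 70% endline-only on the plan's variance, or about 47% / 61% / 75% / 92% as DID at assumed r = 0 / 0.3 / 0.5 / 0.7.

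In either case, state the assumed baseline prevalence, correlation and design effect beside the power figure, and settle the choice before endline data are seen. The cost is wording in two sections and a restated power figure. No extra women are needed.
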